### Plans to promote participant retention and complete follow-up {18b}

Data will be entered at each visit, by a study nurse, and checked periodically for completion by the primary study coordinator. Participant vaccine diary cards are checked for completion and can be completed by a study nurse by telephone if needed. Participants will be contacted to schedule follow-up visits in the event of non-attendance.

### Data management {19}

All clinical trial data will be stored in a password-protected, encrypted, study-specific, online clinical trial management system (CTMS) hosted by the sponsor, Monash University. The CTMS includes the electronic CRF, adverse event, EQ-5D-5L and protocol deviation forms. A paper version of the CRF will be available where a digital version is not. Data will be entered into the CTMS by trained study nurses. Participant-reported data from electronic diary cards will populate a linked patient-reported measurement system (PRMS). Data will be stored indefinitely, backed up regularly, and only accessible by researchers involved in this study. Regular data quality checks will be performed to identify data that appear inconsistent, incomplete, or inaccurate, by trained study coordinators.

### Confidentiality {27}

Participant confidentiality will be strictly maintained by the participating investigators and research staff. Participants will be allocated a participant identification number at enrolment, with personal identifiers maintained in a separate database. This confidentiality will be extended to cover testing of biological samples and genetic tests in addition to the clinical information relating to participants. Password protection and user right management will be used for the CTMS, ensuring only authorized study personnel have access to the data during and after the study.

The trial protocol, documentation, data, and all other information generated will be held in confidence. No information concerning the study, or the data will be released to any unauthorised third party, without prior written approval of the sponsoring institution. No personal identifiers will be reported in publications or presentations.

### Plans for collection, laboratory evaluation and storage of biological specimens for genetic or molecular analysis in this trial/future use {33}

Stored samples may be used for future analyses related to COVID-19 research, including genetic testing and HLA-typing, conditional to adherence to local regulations and ethical guidelines. Genetic testing will be for research purposes and not suitable for clinical purposes and therefore the results, regardless of the findings, will not be returned to the participant.

All future collaborations using biological or other specimens would require approval by the steering committee and need to obtain relevant ethics approval and materials transfer agreement. If any laboratory specimens or other records leave a study site, they will be identified only by the Participant Identification Number to maintain confidentiality.

## Statistical methods

### Statistical methods for primary and secondary outcomes {20a}

Baseline demographic and anthropometric data as well as the defined safety and immunogenicity outcome measures will be stratified by study cohort (HIV, SOT, haematological malignancy) and summarised with appropriate measures of spread. Immune responses and reactogenicity to COVID-19 vaccines will be assessed on a modified intention-to-treat population, depending on actual intervention received between randomisation and providing blood samples for the primary endpoint. Participants with SARS-CoV-2 infection or antibody therapy (e.g. IVIG), between randomisation and providing blood samples will be excluded from the primary analysis. For safety reporting, participants will be included in the intervention group that they received, irrespective of the intervention they were randomised to.

The primary outcome will be the anti-spike IgG antibody against SARS-CoV-2, 21–35 days after completion of study vaccines, summarised as the GMC. Participants who miss a study blood draw, have SARS-COV-2 infection diagnosed by RAT, PCR or anti-nucleocapsid antibodies, or obtain an unscheduled dose of COVID-19 vaccine between the time of randomisation and the primary endpoint will be excluded from analysis. A Bayesian hierarchical two-part model will be used for the primary analysis as it is anticipated that a significant proportion of primary outcomes may be below the assay limit of detection.

Secondary endpoints described above will be analysed depending on the type of outcome; continuous immunological variables will be modelled with the two-part Bayesian model described; binary endpoints, including safety endpoints, will be analysed using a Bayesian logistic model; a Bayesian Poisson regression will be used to compare counts and rates. Further statistical detail is available in the statistical appendix which will be published separately.

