### Eligibility criteria {10}

Inclusion criteriaAble to give informed consent and undertake study proceduresAge ≥ 16 years oldHave completed 3 to 7 doses of Australian Therapeutic Goods Administration (TGA)-approved SARS-CoV-2 vaccine (including mRNA [Pfizer or Moderna], ChAdOx1 [Oxford/Astra Zeneca] or protein [Novavax]) at least 3 months priorFit the criteria to be included in one of the three following ICH groups:ο Infected with HIVο Recipient of a SOT including kidney, pancreas, liver, heart, lung, or combination of these organs at least 6 weeks prior and without episodes of severe rejection requiring T- or B-cell depleting agents in the prior 3 monthsο Undergoing chemotherapy, immunotherapy and/or targeted therapy, or completed in the last 2 years for chronic lymphocytic leukaemia (CLL), non-Hodgkin lymphoma (NHL), or multiple myeloma (MM).

Exclusion CriteriaContraindicated to receive a COVID-19 booster vaccine (e.g. history of anaphylaxis to a vaccine component or myocarditis attributed to previous receipt of an mRNA vaccine).Has had less than 3 or more than 7 doses of COVID-19 vaccineIs on another clinical trial investigating alternate COVID-19 vaccination schedules or investigational drugs to prevent or treat COVID-19Life expectancy < 12 months or enrolment deemed not in the best interest of the patientUnable to provide informed consentReceipt of SARS-CoV-2 specific monoclonal antibodies in the 3 months prior to receiving the first dose of study vaccineAcute respiratory tract infection and/or temperature > 38 degrees on the day of receipt of the first dose of the study vaccineHistory of autologous stem cell transplant in the prior 6 months or history of ever having an allogeneic stem cell transplant or CAR T-cell therapyHave not received another licensed vaccine in the 7 days before or plan to receive one in the 7 days after the day of receiving the COVID-19 study vaccine (note: participants can receive another licensed vaccine on the same day as the COVID-19 vaccine)

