### Sample size {14}

The maximum sample size is 960 participants, including 320 in each of the HIV, SOT, and haematological malignancy groups. This maximum sample size is based on simulations conducted prior to trial commencement for estimating the primary outcome (anti-spike SARS-CoV-2 IgG antibodies 28 days after completion of trial vaccine/s) for different trial strata (clinical group [HIV, SOT, haematological malignancy], vaccine brand, SARS-CoV-2 serostatus at enrolment) with sufficient precision. The simulations are detailed in the Statistical Appendix and will be published separately.

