### Interim analyses {21b}

The first analysis of the primary outcome will be performed after 260 eligible participants have completed 21–35 days of follow-up after receipt of their final study vaccine, and the results from the batched blood samples are available from the laboratory analysis. Subsequent analyses will be performed after every 100 additional participants have available laboratory results for the remainder of the trial until the maximum recruitment of 960 participants is reached.

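### Immunoglobulin given before randomisation stays in the anti-spike IgG endpoint, and the exclusion for later immunoglobulin spans about 28 days in one-dose arms but about 112 days in two-dose arms

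*Protocol article*

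**What the plan says.** The endpoint is an antibody concentration: "The primary outcome will be the anti-spike IgG antibody against SARS-CoV-2, 21–35 days after completion of study vaccines, summarised as the GMC" (Protocol article, Statistical methods {20a}).

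The same section sets the rule on antibody therapy: "Participants with SARS-CoV-2 infection or antibody therapy (e.g. IVIG), between randomisation and providing blood samples will be excluded from the primary analysis". A second list of exclusions follows. It covers missed blood draws, infection, and participants who "obtain an unscheduled dose of COVID-19 vaccine between the time of randomisation and the primary endpoint will be excluded from analysis". It does not mention antibody therapy.

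The only antibody-related item under Eligibility criteria {10} excludes people given monoclonals directed at SARS-CoV-2 within 3 months of the first study dose. Neither the inclusion nor the exclusion list mentions IVIG or other immunoglobulin replacement, so recipients may enter any of the three groups. One of these is people under treatment, or treated in the past 2 years, for CLL, NHL or myeloma.

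Table 1 puts the visit about a month after vaccination at day 28 (±7) for one dose and at day 112 (±7) for two doses. On numbers, Sample size {14} says: "The maximum sample size is 960 participants, including 320 in each of the HIV, SOT, and haematological malignancy groups". It adds: "The simulations are detailed in the Statistical Appendix and will be published separately".

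**The concern.** The plan names IVIG as a reason to discard a primary-endpoint value, so it accepts that donor antibody can be read as vaccine response. Two gaps follow from how the rule is timed.

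- **No look-back.** Immunoglobulin given shortly before randomisation is caught neither at screening nor in the analysis, although the eligibility criteria apply a 3-month look-back to monoclonals. What remains at sampling depends on elapsed time, and the one-dose sample comes about 84 days earlier than the two-dose sample.
- **Unequal windows.** The post-randomisation rule runs to the endpoint sample, so it covers about four times as many days in two-dose arms. The same infusion schedule can leave a participant evaluable under one allocation and excluded under the other.

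Both bear on the comparison of one with two doses. Comparisons between vaccines at the same number of doses share a sampling time, so the carry-over is balanced there in expectation, although the absolute GMCs would still include it.

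**Working it through.** **The plan's own figures.** 3 × 320 = 960, and 260 + 7 × 100 = 960, so the maximum and the interim schedule agree. The 320 per group comes from simulations whose inputs are not in the article, so it cannot be re-derived.

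**Inputs from the article.** One-dose sample at day 28 (21–35); two-dose sample at day 112 (105–119).

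**Assumptions, not in the article.** Randomisation falls at or close to dose 1. The product contains anti-spike IgG, as the plan's own exclusion implies. IgG half-life h is 21–28 days. A regular recipient is infused every T days with random phase.

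**Step 1: passive antibody remaining from an infusion just before randomisation.** Fraction = 0.5^(t/h).

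| h (days) | t = 28 | t = 112 |
|---|---|---|
| 14 | 25% | 0.4% |
| 21 | 40% | 2.5% |
| 28 | 50% | 6.2% |
| 35 | 57% | 11% |

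The middle rows are the main assumption and the outer rows a wider range. In every row the one-dose sample carries several times more residue than the two-dose sample.

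**Step 2: chance that a regular recipient stays in the primary analysis.** P(no infusion in W days) = max(0, 1 − W/T).

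| T (days) | One dose: W = 21 / 28 / 35 | Two doses: W = 105 to 119 |
|---|---|---|
| 21 | 0 / 0 / 0% | 0% |
| 28 | 25 / 0 / 0% | 0% |
| 42 | 50 / 33 / 17% | 0% |
| 84 | 75 / 67 / 58% | 0% |

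In two-dose arms the chance is zero for any interval up to 105 days. In one-dose arms it is zero or small at intervals of about 4 weeks or less and rises with longer ones.

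**Step 3: would a 3-month look-back be long enough?** Table 1 counts 3 months as 84 days. An infusion exactly 84 days before dose 1 is 84 + 28 = 112 days old at the one-dose sample. The residue is then 2.5–6.2%, the level in the t = 112 column above. Anyone already on replacement every 84 days or less has an infusion inside the look-back, and so is identified whatever the allocation.

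**The case against.** The strongest reply has four parts.

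- **The article is condensed.** Analysis sets and the handling of concomitant immunoglobulin may be detailed in the Statistical Appendix. That is a fair reason not to complain about missing detail. But the article does state a rule, with a defined start and end, and the problem lies in that timing. An attrition allowance in the simulations would cure neither the look-back gap nor the unequal windows.
- **The trial can partly see passive antibody.** Anti-spike IgG is measured at baseline, enrolment serostatus is a stratum, and interactions with it may be examined. This helps, but a baseline value does not separate donor antibody from the participant's own, and the two decay differently up to days 28 and 112.
- **Randomisation balances earlier IVIG.** True at baseline. It does not balance the residue at two different sampling times.
- **The two gaps mostly concern different people.** This stands. A regular recipient infused before randomisation is usually removed by the next infusion, so carry-over is kept mainly in one-off, recently stopped or long-interval recipients.

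A reader might infer more than the documents support. That regular recipients can never contribute is too strong: Step 2 shows that some remain in one-dose arms, and the exclusion concerns the primary analysis only. A fixed loss in the haematology group is not established either. The article gives no prevalence of replacement and the rule covers all three groups. Moreover, 320 is a cap under a precision-based stopping rule, so short of the cap exclusions lengthen recruitment rather than widen the interval. A percentage inflation of the GMC would need the share of carriers and their rise in titre, and neither is given. Leaving recipients out of the count toward 320 would simply mean enrolling more people, and the documents do not show a need for it.

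**Conclusion.** The point holds for the timing of the rule. As written, immunoglobulin given shortly before randomisation stays in the primary endpoint. At an assumed half-life of 21–28 days, about 40–50% of it is present at the one-dose sample and about 2.5–6% at the two-dose sample, so the carry-over raises one-dose GMCs relative to two-dose GMCs. The size of that shift cannot be derived from the article.

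Separately, exclusion for immunoglobulin after randomisation depends on the assigned schedule. Regular recipients are rarely evaluable after one dose if infused about every 4 weeks or more often, more often evaluable at longer intervals, and effectively never evaluable after two doses. The direction of the resulting selection is not fixed, because it depends on how these participants respond to vaccination.

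**What to change.** 1. Record at baseline any immunoglobulin or other antibody therapy, with its date and whether it is scheduled replacement.
2. In Statistical methods {20a}, add an exclusion from the primary analysis based on pre-randomisation information and applied identically in all arms: IVIG or other antibody therapy in the 3 months before dose 1, or scheduled replacement at baseline. Keep the existing post-randomisation rule.
3. Reconcile Eligibility criteria {10} with {20a}, so that it is explicit that recipients may enrol and how each analysis treats them. Keep them in the safety, T-cell and clinical outcomes.
4. Add a sensitivity analysis of the primary endpoint that retains these participants.

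The cost is a baseline question, a few sentences and one extra analysis, with slightly fewer participants in the primary set. Many of those removed would already be lost under the current rule. The added loss is mainly one-off or recently stopped recipients, plus regular recipients in one-dose arms who would otherwise have stayed in. One imbalance remains: people who start immunoglobulin after randomisation still face the longer window in two-dose arms, and the sensitivity analysis is the check on that.

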**Methods:**

Bringing optimised COVID-19 vaccine schedules to immunocompromised populations (BOOST-IC) is an adaptive randomised trial of one or two additional doses of COVID-19 vaccines 3 months apart in people living with HIV, solid organ transplant (SOT) recipients, or those who have haematological malignancies (chronic lymphocytic leukaemia, non-Hodgkin lymphoma or multiple myeloma). Key eligibility criteria include having received 3 to 7 doses of Australian Therapeutic Goods Administration (TGA)-approved COVID-19 vaccines at least 3 months earlier, and having not received SARS-CoV-2-specific monoclonal antibodies in the 3 months prior to receiving the study vaccine. The primary outcome is the geometric mean concentration of anti-spike SARS-CoV-2 immunoglobulin G (IgG) 28 days after the final dose of the study vaccine. Key secondary outcomes include anti-spike SARS-CoV-2 IgG titres and the proportion of people seroconverting 6 and 12 months after study vaccines, local and systemic reactions in the 7 days after vaccination, adverse events of special interest, COVID-19 infection, mortality and quality of life.

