### Criteria for discontinuing or modifying allocated interventions {11b}

Participants may discontinue participation or withdraw their consent without penalty. An investigator may also discontinue a participant from trial intervention if the participant demonstrates significant non-compliance with the trial intervention; experiences a serious or intolerable adverse event such that continued trial intervention would not be in the best interest of the participant; or requires early discontinuation for any other reason.

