### Outcomes {12}

The primary outcome is defined as the geometric mean concentration (GMC) of anti-spike IgG antibody against SARS-CoV-2, 28 days after completion of trial vaccine/s, i.e. after one or two doses in the respective trial arms.

Secondary outcomes include laboratory, safety and clinical outcomes:

Laboratory outcomesThe GMC of anti-spike IgG antibody against SARS-CoV-2, 6 and 12 months after completion of trial vaccine/sThe proportion of participants seropositive to SARS-CoV-2 IgG, 1, 6 and 12 months after completion of trial vaccine/sThe GMC of anti-spike IgG antibody targeting specific SARS-CoV-2 variants, 1, 6 and 12 months after completion of trial vaccine/sThe SARS-CoV-2 neutralising antibody response, 1, 6 and 12 months post completion of trial vaccine/s, in a subset of participants with response defined as either rise in the neutralising antibody titreο Fourfold rise in the neutralising antibody titre for those with detectable neutralising antibodies at baseline, ORο Detectable neutralisation in those with no detectable neutralising antibodies at baselineThe magnitude of SARS-CoV-2 specific T-cell responses, 1, 6 and 12 months post completion of trial vaccine/s in a subset of participantsSubset analysis and polyfunctionality (number of effector cytokines) of SARS-CoV-2 specific T-cell responses, 1, 6 and 12 months post completion of trial vaccine/s in a subset of participants

Safety outcomesLocal and systemic reactions assessed on days 1, 2, 3, 4, 5, 6 and 7 after randomisation.Hospitalisation resulting from adverse events following immunisation (AEFI) up to day 28.Adverse events of special interest (AESI) up to 12 months post completion of trial vaccine/s

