### Methods in analysis to handle protocol non-adherence and any statistical methods to handle missing data {20c}

No modifications or corrections to the endpoint will be made due to non-adherence to allocated intervention, in the context of a serious adverse event, or where non-adherence is due to site procedures or availability. In contrast, participants with missing data (e.g. blood draw) due to lost to follow-up or withdrawal from the study will be excluded from the analyses.

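### Grouping safety by intervention received, if it extends to number of doses, moves dose-1 reactors who miss dose 2 into the one-dose group and biases schedule comparisons towards two doses

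*Protocol article*

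**What the plan says.** All references are to the Protocol article.

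- **Safety grouping, section {20a}:** "For safety reporting, participants will be included in the intervention group that they received, irrespective of the intervention they were randomised to". The same section assesses reactogenicity in a modified intention-to-treat population, "depending on actual intervention received between randomisation and providing blood samples for the primary endpoint".
- **Arms, Abstract (Methods) and section {12}:** the trial compares "one or two additional doses of COVID-19 vaccines 3 months apart", and the primary outcome is timed from the last dose, "i.e. after one or two doses in the respective trial arms". Number of doses is therefore part of what defines an arm.
- **Stopping, section {11b}:** an investigator may discontinue the intervention for a participant who "experiences a serious or intolerable adverse event such that continued trial intervention would not be in the best interest of the participant". Participants may also stop of their own accord.
- **Blinding, section {17a}:** participants learn after the 1-month visit whether a second dose is due.
- **Safety outcomes, section {12}:** daily local and systemic reactions in the first week after randomisation, "Hospitalisation resulting from adverse events following immunisation (AEFI) up to day 28", and adverse events of special interest up to 12 months after the last dose.
- **Model, section {20a}:** "binary endpoints, including safety endpoints, will be analysed using a Bayesian logistic model".
- **Non-adherence, section {20c}:** "No modifications or corrections to the endpoint will be made due to non-adherence to allocated intervention, in the context of a serious adverse event".

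**The concern.** As-received grouping is the usual choice for safety when arms are different products, because a participant given the wrong vaccine should be counted under that vaccine. It works differently when one arm's treatment is the first part of the other's. Every two-dose participant passes through the one-dose state. Whether they leave it can depend on how they tolerated dose 1, which is the outcome being measured.

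Movement caused by a reaction goes one way only. A two-dose participant who reacts and stops becomes a one-dose participant, but a one-dose participant has no matching route into the two-dose group. Events leave the two-dose group and enter the one-dose group, so the direction of the bias is known.

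The early endpoints are the most exposed. Dose 2 is scheduled at day 84 with a window of 7 days either side (Table 1). Reactions in the first week after randomisation therefore precede it, as do hospitalisations to day 28 if that window also runs from randomisation. Over that period both schedules have had the same exposure. A systematic difference between them could come only from the regrouping. For endpoints that run past dose 2, the same shift could hide a real excess caused by the second dose.

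**Working it through.** The article states no figure for this point, so there is none to reproduce. The check is algebra over a range of assumptions.

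**Inputs**
- Maximum sample size 960 (section {14}) with equal allocation (section {16a}). I take 960 / 2 = 480 per schedule. The even split is an assumption.
- r = dose-1 event risk, the same in both randomised schedules. Assumed 3%, so 480 × 0.03 = 14.4 expected events in each.
- d = share of two-dose participants with an event who then get no dose 2. Not given, so a range is shown.
- At first, nobody misses dose 2 for any other reason.

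**Formulas, grouped as received**
- Moved from two-dose to one-dose: 480·r·d
- One-dose rate = r(1 + d) / (1 + rd)
- Two-dose rate = r(1 − d) / (1 − rd)
- Only participants with events move, so each group keeps 480 − 14.4 = 465.6 non-events. The odds ratio is therefore (1 − d) / (1 + d), whatever the value of r.

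**Results (true odds ratio 1.00)**

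| d | Moved | One-dose | Two-dose | OR |
|---|---|---|---|---|
| 5% | 0.72 | 15.12/480.72 = 3.15% | 13.68/479.28 = 2.85% | 0.90 |
| 10% | 1.44 | 15.84/481.44 = 3.29% | 12.96/478.56 = 2.71% | 0.82 |
| 1/3 | 4.8 | 19.2/484.8 = 3.96% | 9.6/475.2 = 2.02% | 0.50 |
| 2/3 | 9.6 | 24.0/489.6 = 4.90% | 4.8/470.4 = 1.02% | 0.20 |

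**Other missed second doses dilute the bias but do not remove it.** Take r = 5% and d = 50%.
- No other misses: 0.075/1.025 = 7.32% one-dose against 0.025/0.975 = 2.56% two-dose, risk ratio 0.35.
- If 10% of non-reactors also miss dose 2 (0.95 × 0.10 = 0.095 of the arm): 0.075/1.12 = 6.70% against 0.025/0.88 = 2.84%, risk ratio 0.42.

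**A real excess can be hidden.** Keep r = 5% and d = 50%, and let dose 2 cause an event in 5% of participants without a dose-1 event.
- As randomised: (0.05 + 0.95 × 0.05)/0.05 = 0.0975/0.05, risk ratio 1.95.
- As received: (0.025 + 0.0475)/0.975 = 7.44% against 7.32%, risk ratio 1.02.

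**After the change.** With everyone given dose 1 grouped by allocated schedule, the dose-1 comparison has expected rates r and r, a ratio of 1.00 for any r and d.

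**The case against.** **The sentence may mean product only.** The article often describes arms by vaccine: section {8} speaks of comparing up to three vaccines, and section {16a} of allocation to vaccine arms. Nowhere does it say how an incomplete two-dose course is classed. A reader might infer that it expressly assigns such participants to the one-dose group. It does not; that follows from reading the safety sentence together with section {12}, which defines arms by number of doses. This stands as a limit on confidence. It does not remove the point, because nothing in the article confines the rule to product.

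**Section {20c} seems to point the other way.** It rules out corrections for non-adherence in the context of a serious adverse event. But it concerns the endpoint, not the group in which the participant is counted. Nor does it mention a reaction that is intolerable without being serious, which section {11b} also accepts as grounds for stopping. The two sections need reconciling, and {20c} does not settle the matter.

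**Detail is left to the statistical appendix.** That is true of table layouts and of how incomplete courses are classed. The as-received rule itself, however, is stated in the article without qualification. Solicited events are already collected after each vaccination (section {22}), so the article does not rule out reporting by dose.

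**The effect may be small.** This stands. Participants have already had 3 to 7 doses, and those with a contraindication are excluded (section {10}). An unrelated hospital presentation counts as serious (section {22}) but need not prevent a dose months later. At d = 5% the expected number moved is below one participant.

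**Safety oversight does not depend on this table.** Serious events are reported to the sponsor and ethics committee within 24 hours, and the monitoring committee reviews safety at least three times a year. Individual events would not be lost. The between-schedule summary would still be distorted.

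**Conclusion.** The point holds on the plain reading and is of moderate importance. Applied to number of doses, the as-received rule makes group membership depend on the dose-1 outcome and biases a schedule comparison of safety in favour of two doses. Comparisons between vaccine products, pooled over schedule, are not affected, because the participant stays with the same product.

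The size cannot be fixed from the article. With 1:1 schedules, equal true risk and no other missed second doses, the odds ratio is (1 − d)/(1 + d): 0.90 and 0.82 if 5% or 10% of events stop dose 2, 0.50 and 0.20 if one third or two thirds do. The 3% risk, the stopping shares and the 480:480 split are all assumptions.

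A reader might go further and infer that the trial is set to declare two doses safer than one. The article does not support that. It puts safety endpoints into a logistic model but names no one-versus-two-dose safety contrast, gives no rates that would make the larger shifts likely, and treats these outcomes as secondary.

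**What to change.** 1. Limit the as-received rule to vaccine product: a participant given a different vaccine from the one allocated is counted under the vaccine given.
2. Keep the number-of-doses group as randomised for everyone who received dose 1, in both the safety and the reactogenicity analyses.
3. Report dose-1 events among all given dose 1, and dose-2 events among all given dose 2.
4. Show, by product and clinical group, how many participants randomised to two doses missed dose 2, and how many of these did so because of an adverse event.
5. Reconcile the safety sentence in {20a} with {20c}, so that both say in which group a participant who stops after an adverse event is counted.

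The cost is wording in the protocol and statistical appendix, plus table shells. Reactions are already collected after each vaccination. The reason for a missed second dose has to be available for item 4; the article does not say whether the case report form records it. Randomisation, sample size and the primary outcome are unchanged.
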